## **8 DATA COLLECTION AND DATA MONITORING**

### **8.1 Data Quality Assurance**

This study will be organized, performed, and reported in compliance with the CRO's Standard Operating Procedures, protocols and working practice documents, and the requirements of national and international GCP and ICH guidelines. Compliance will be achieved through a combination of study specific audits of the investigational site and of the CRO's systems for data handling, analysis, and reporting.

### **8.2 Case Report Form and Source Documentation**

The investigator or appropriate designee will enter the information required by the protocol onto a CRF for each subject. A CRF manual will be provided to assist in correct CRF completion. Study participants must not be identified by name on any study documents. Upon enrollment, subjects will be assigned and identified by subject identification numbers.

Any data that are recorded on the CRFs without any prior written or electronic record must have the source clearly identified.

### **8.3 Data Management**

Data from CRFs and other external data will be entered into a clinical database as specified in the CRO's data management plan. Quality control and data validation procedures will be applied to ensure the validity and accuracy of the clinical database.

Data from CRFs and other external data will be reviewed and checked for omissions, apparent errors, and values requiring further clarification using computerized and manual procedures. Data queries requiring clarification will be documented and returned to the investigational site for resolution. Only authorized personnel will make corrections to the clinical database, and all corrections will be documented in an audit trail.

### **8.4 Data Monitoring**

After study initiation, the investigational site will be visited by the CRO on behalf of the Sponsor to review the CRFs and source documents for completeness, accuracy, protocol compliance, subject safety, and adherence to guidelines outlined in the Study Operations Manual. The CRO representative will highlight any discrepancies found between source documents and the completed CRFs and ensure that appropriate site personnel address the discrepancies. When a discrepancy results in corrected CRF data, the correction

will be initialed and dated on the CRF. Uniform procedures will be discussed at the site initiation.

## **9 STATISTICAL ANALYSIS**

The statistical analyses described in this section will be performed as further outlined in the Statistical Analysis Plan (SAP), which will be finalized prior to completion of the clinical portion of the study and will be included in the Clinical Study Report for this protocol. The SAP will give a detailed description of the summaries and analyses (primary and secondary) that will be performed. Changes from analyses planned in the protocol will be documented in the SAP. If changes to principal features stated in the protocol are required, these will be documented in a protocol amendment.

All variables will be summarized at specified time points by dose level. Categorical variables will be summarized using counts (n) and percents (%) and will be presented in the form n (%). Continuous variables (eg, height, weight) will be summarized using the number of observations, mean, standard deviation and/or standard error, and minimum and maximum values.

### **9.1 Analysis Populations**

The following subject subsets will be defined for this study.

- Safety population: the set of subjects who received at least 1 dose of investigational product and have any follow-up information. All safety analyses, including analyses of AEs, clinical laboratory results, vital signs, and physical examinations will be conducted on the Safety population.
- Efficacy population: the set of subjects who received at least 1 dose of investigational product and at least 1 IVM measurement. The primary and secondary efficacy analyses will be performed on subjects from this population.
- PK population: The set of subjects who receive at least 1 dose of investigational product and who have sufficient post-dose blood samples taken to estimate  $C_{\max}$  and AUC.

### **9.2 Statistical Methods**

#### **9.2.1 Subject Disposition**

The disposition of subjects at all scheduled visits will be determined on the basis of evaluations made at each visit. The disposition will be summarized by dose level.

### **9.2.2 Demographics and Baseline Characteristics**

Demographic and baseline information will be summarized using mean, standard deviation, and minimum and maximum values for continuous variables and the number and percentages for categorical variables.

Demographics and subject characteristics obtained at the baseline evaluation will be summarized descriptively using the Safety population. Demographics by dose level will be summarized with the following information: age, genotype, race, ethnicity, and weight.

Due to the small sample size, no inferential tests will be performed to statistically compare the dose levels on demographics and baseline characteristics.

### **9.2.3 Efficacy**

The primary efficacy analysis will be performed on the Efficacy population. For the final analysis, mean microvascular blood flow and change from baseline will be summarized by time point. Change from baseline microvascular blood flow will be modeled longitudinally using a mixed effects model with a random subject effect and baseline microvascular blood flow and treatment as fixed effects.

Secondary efficacy outcome measures will include biomarkers of adhesion, inflammation, and downstream selectin effect in the blood. All of these secondary measurements will be analyzed using a mixed model similar to the primary efficacy endpoint.

### **9.2.4 Safety Data**

Safety endpoints will be summarized by cohort and descriptively analyzed for differences across cohorts using a Fisher's Exact Test as the data allow. All AEs, including SAEs, will be coded using the MedDRA dictionary. A by-subject listing of all AEs will be provided. Summaries will be provided for each of the following types of AEs:

- Treatment-emergent AEs (TEAEs);
- Treatment-emergent SAEs;
- Treatment-emergent SAEs that were reported as “possibly”, “probably”, or “definitely” related to study drug;
- TEAEs that were reported as “possibly”, “probably”, or “definitely” related to study drug;
- TEAEs by severity;
- TEAEs that lead to discontinuation of the study;
- TEAEs resulting in death.

TEAEs will be defined as those AEs that begin on or after the date/time of study drug administration. Drug-related AEs will include those AEs that are reported by the investigator as possibly, probably, or definitely related to the study drug. With the exception of the TEAEs by severity summary, all summaries will present the number of AEs and the number and percent of subjects having an AE by system organ class and by specific AE preferred term. The TEAEs by severity summary will only report the number and percent of subjects. For all percentages, the subjects in the Safety population by dose level will comprise the denominator.

In addition to these summary tables, subjects with treatment-emergent SAEs and subjects who discontinued prematurely due to a TEAE will be presented in separate subject listings. The listings will provide all of the information reported for that AE and will include the length of time from study drug administration to the occurrence of the AE. If any deaths occur in the study, a similar listing of all TEAEs for subjects who died will be provided.

### 9.2.5 Pharmacokinetic Analysis

Due to the limited number of plasma concentrations, PK parameters will be estimated by fitting a compartmental model derived from richer datasets in healthy volunteers (Studies GMI-1070-101 and GMI-1070-102).

PK parameters to be estimated will include:

|                  |                                                                         |
|------------------|-------------------------------------------------------------------------|
| CL               | Total plasma clearance                                                  |
| CL D2 | Clearance from the peripheral (non-central compartment)                 |
| V 1   | Volume of the central compartment                                       |
| V 2   | Volume of the peripheral (non-central compartment)                      |
| C max | Maximum observed drug concentration                                     |
| t max | Time of the maximum drug concentration (obtained without interpolation) |
| α                | Apparent distribution rate constant                                     |
| β                | Apparent terminal elimination rate constant                             |
| t 1/2 | Apparent elimination half-life, calculated as ln(2)/β                   |

### **Urine**

PK parameters will be computed from the individual urine concentrations using a noncompartmental approach. Appropriate validated PK software (eg, WinNonlin Professional) will be used.

|             |                                                                                                                                                                     |
|-------------|---------------------------------------------------------------------------------------------------------------------------------------------------------------------|
| $U_e$       | The amount excreted in urine during each collection interval ( $C_{urine}$ ), calculated as $C_{urine} \times$ urine volume.                                        |
| $CL_r$      | Renal clearance, calculated as $CL_r = U_e/AUC_{0-t}$ . $CL_r$ will be calculated for each collection interval and for the entire 8-hour steady-state study period. |
| $Cum_{U_e}$ | Cumulative amount excreted in urine over the urine collection period.                                                                                               |
| % Dose      | The percentage of drug recovered in urine, calculated as $(Cum_{U_e})/Dose \times 100$ .                                                                            |

### ***Analysis of Pharmacokinetics***

The secondary endpoint is the PK of the multiple doses of IV GMI-1070 as given in this study.

PK parameters will be summarized by dose level using descriptive statistics (arithmetic means, standard deviations, coefficients of variation, sample size [N], minimum, maximum and median). Figures will be created to display mean and individual (observed and model-predicted) analyte concentration-time curves.

Additional analyses will be performed as deemed necessary upon review of the data.

#### **9.2.6 Vital Signs and Laboratory Parameters**

For vital signs and continuous laboratory parameters, the observed value and the change in the value from baseline at each collection point during the treatment phase will be presented. Values will be analyzed using a generalized linear mixed model over the longitudinal measurements. This model will allow comparisons of each secondary outcome over the treatment groups, controlling for time and baseline measurement as fixed effects and subject as a random effect.

For categorical laboratory parameters that are collected in terms of abnormal or normal or can be classified into positive or negative results, the number and percent of subjects having values in each category will be presented at each scheduled collection time. For those categorical laboratory parameters that are reported in several descriptive categories (eg, urinalysis color), the number and percent of subjects by each category will be presented. Graphs displaying population trends over time may be produced.

For both vital signs and laboratory parameters, clinically significant results will be listed with relevant subject information for assessment.

#### **9.2.7 Physical Examinations**

Significant changes in physical examination over the study visits will be listed by subject and summarized across the study population as appropriate.

#### **9.2.8 Investigational Product Interim Analysis**

An interim analysis will be performed by site. An interim analysis will be done after every fourth subject at each clinical site completes the study to determine whether to change the dose level for the next group of 4 at that site. These 4 subjects will be examined to determine whether the dose of GMI-1070 was safe and effective (see Section 6.2.5). PK data will also be analyzed at this time. This analysis will be repeated for each group of 4 subjects at the clinical site level.

### **9.3 Statistical Considerations**

#### **9.3.1 Missing Data**

Subjects with missing outcome data will not be included in the analysis. Subjects who drop out of the study prior to obtaining endpoint data from hour 24 will be replaced by the next available subject (see Section 4.4).

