#### **4.4 Withdrawal of Subjects**

A subject is free to withdraw from the study at any time for any reason without prejudice to their future medical care by the physician or at the institution. The investigator or Sponsor may also withdraw the subject at any time in the interest of subject safety. The primary reason for withdrawal must be recorded on the withdrawal form in the case report form (CRF). If a subject is withdrawn for more than 1 reason, each reason should be documented and the most medically significant reason should be noted on the CRF.

The withdrawal of a subject from the study should be discussed where possible with the Medical Monitor before the subject stops investigational product. If investigational product is discontinued, the final evaluations will be performed as completely as possible. Subjects who drop out of the study prior to obtaining endpoint data from hour 24 will be replaced by the next available subject. Any comments (spontaneous or elicited) or complaints made by the subject and the reason for termination, date of stopping investigational product, and the total amount of investigational product taken must be recorded in the CRF.

The Sponsor reserves the right to terminate the study at any time.

Reasons for withdrawal may include:

- If consent is withdrawn or the subject refuses to continue treatment and/or procedures/observations
- If the clinical condition under study requires alternative treatment
- Occurrence of unmanageable AEs or if the subject requires concomitant medication disallowed under this protocol (see Section 5.2)
- If the subject becomes pregnant
- For other reasons (eg, significant protocol violation or non-compliance)

At least 3 documented attempts must be made to contact any subject lost to follow-up, 1 of which must include sending a certified letter to the subject's last

known address, requesting that they return to the study site for final safety evaluations.

The Sponsor may be contacted if clarification is required on a case-by-case basis.

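### The missing-data sentence in Section 9.3.1, read plainly, drops subjects whom the Efficacy population in Section 9.1 includes and whose partial records the mixed model in Section 9.2.3 could use

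*Protocol*

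**What the plan says.** **Exclusion.** Protocol Section 9.3.1: "Subjects with missing outcome data will not be included in the analysis". It does not define missing outcome data (any time point, a key time point, or everything), and it does not say which analysis is meant.

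**Replacement.** Sections 4.4 and 9.3.1 both say: "Subjects who drop out of the study prior to obtaining endpoint data from hour 24 will be replaced by the next available subject". The reason for leaving plays no part. Section 4.4 lists "Occurrence of unmanageable AEs" among the reasons for withdrawal.

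**Efficacy population.** Section 9.1: "the set of subjects who received at least 1 dose of investigational product and at least 1 IVM measurement". It adds: "The primary and secondary efficacy analyses will be performed on subjects from this population".

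**Efficacy model.** Section 9.2.3: "Change from baseline microvascular blood flow will be modeled longitudinally using a mixed effects model with a random subject effect", with baseline flow and treatment as fixed effects. For the biomarkers: "All of these secondary measurements will be analyzed using a mixed model similar to the primary efficacy endpoint".

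**Size and schedule.** Sections 3 and 6.2.2 set 6 IVM times (predose, 30 minutes, and 2, 4, 8 and 24 hours). Section 3 continues until 20 subjects have been treated.

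**The concern.** Sections 9.1 and 9.3.1 give different answers to the same question: is a subject with five of six IVM values in the efficacy analysis? Section 9.1 says yes. Section 9.3.1, on its plain reading, says no. Two programmers working from this protocol could produce different datasets and both claim to have followed it.

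The exclusion also works against the purpose of the model. A longitudinal model with a random subject effect, fitted by likelihood, uses each subject's observed values and gives valid estimates if data are missing at random. Deleting whole subjects gives up that advantage. It costs precision in a study of only 20, with groups of 4, and it can bias the estimate if those with gaps differ from those without.

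Gaps related to the subject's condition are plausible here. Hour 24 is an outpatient return visit, Section 7.4 anticipates vaso-occlusive crises within 24 hours of dosing, and withdrawal for an adverse event is foreseen. Such a subject would leave the efficacy analysis and another would be enrolled instead.

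**Working it through.** **Step 1. Possible meanings of the exclusion.**

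| Meaning of missing outcome data | Agrees with Section 9.1? |
|---|---|
| (a) Any of the 6 IVM values is missing | No. A subject with 5 of 6 values is in the population but not in the analysis |
| (b) The hour-24 value is missing | No. A subject measured through 8 hours is in the population but not in the analysis |
| (c) No IVM data at all | Yes, but the sentence then adds nothing to Section 9.1 |

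Only (c) avoids the conflict, and the text does not say it.

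**Step 2. How many subjects would be lost.** The protocol states no missing rate, drop-out rate, effect size or SD, so there is no figure to reproduce. The rates below are assumptions.

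Inputs: n = 20 (Section 3); k = 6 IVM times (Sections 3 and 6.2.2); m = assumed chance that one value is missing, independent across times.

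Reading (a): P(subject complete) = (1 − m)^6, and expected subjects kept = 20 × (1 − m)^6. Reading (b): expected subjects kept = 20 × (1 − m).

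| m | P(complete) | Kept of 20, reading (a) | P(group of 4 all complete) = P(complete)^4 | Kept of 20, reading (b) |
|---|---|---|---|---|
| 2% | 0.98^6 = 0.886 | 17.7 | 0.616 | 20 × 0.98 = 19.6 |
| 5% | 0.95^6 = 0.735 | 14.7 | 0.292 | 20 × 0.95 = 19.0 |
| 10% | 0.90^6 = 0.531 | 10.6 | 0.080 | 20 × 0.90 = 18.0 |

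**Step 3. How many valid measurements would be thrown away under (a).** The schedule yields 20 × 6 = 120 values. At m = 5%, 120 × 0.95 = 114 are expected to be observed, and 120 × 0.735 = 88.2 belong to complete subjects. So 114 − 88.2 = 25.8 observed values would be discarded.

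**Step 4. Replacement.** Let q be an assumed chance of dropping out before hour-24 data. P(at least one in a group of 4) = 1 − (1 − q)^4. Subjects dosed to obtain 20 completers = 20/(1 − q), rounded up.

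| q | At least one in a group of 4 | Dosed for 20 completers |
|---|---|---|
| 5% | 0.19 | 22 |
| 10% | 0.34 | 23 |
| 20% | 0.59 | 25 |

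Replacement would therefore not be a rare event. How replaced subjects are counted matters, and the wording differs between sections: Section 3 speaks of subjects treated, Section 6.2.5 of subjects studied with 48-hour data as available, and Section 9.2.8 of every fourth subject completing the study. None of them says where a replaced subject stands.

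**Step 5. Can deletion bias the result?** A simulation (300 runs, 20 subjects, 5 post-dose visits, true hour-24 change 0.5, between-subject SD 1, residual SD 0.7, low responders at the third post-dose visit more likely to drop out) gave a mean hour-24 estimate of 0.48 from a mixed model on all available data. Whole-subject deletion gave 0.65 and kept 16.3 subjects on average. This shows that bias is possible. Its sign follows from the assumption about who drops out, and nothing in the protocol supports that assumption over the opposite one.

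**The case against.** **The clash with the model is not a formal one.** A mixed model can be fitted to complete subjects, so Sections 9.2.3 and 9.3.1 can both be obeyed. This stands. The textual conflict is with Section 9.1; with Section 9.2.3 it is one of purpose.

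**The losses may be small.** Five of the six IVM times fall on the dosing day in the clinic, so independent missingness is doubtful. The sentence after the exclusion speaks of hour-24 data, which favours reading (b) and about 19 of 20 kept at 5% missing. This also stands, and the figures for reading (a) are an upper illustration. The conflict remains under (b).

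**The analysis plan may define the term.** It may, and efficacy is secondary to safety in this largely descriptive study. That lowers the severity, but the protocol sentence as it stands is still inconsistent.

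**A stronger reading is tempting:** a reader might infer that subjects who did not tolerate the drug vanish from the safety results, or that each dose review sees only the four who tolerated it, so that a dose looks safer and more effective than it is. The documents do not support this.

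- Section 9.1 keeps every dosed subject with any follow-up in the Safety population and runs all safety analyses there.
- Section 9.2.4 uses that population as the denominator for adverse event percentages, and requires a summary and a listing of events leading to discontinuation.
- Section 6.2.5 reviews each subject's 48-hour data as available, including adverse events.
- The halting rules in Section 7.4 are triggered by events, and replacing a subject cancels none of them.
- No section links tolerability to blood-flow response, so a bias towards greater effect is not shown.

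Two things remain of it. The exclusion is unqualified, so its reach into the longitudinal vital-sign and laboratory models of Section 9.2.6 should be ruled out in words. And whether a replaced subject belongs to the group of 4 is ambiguous, which is not the same as a stated exclusion.

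**Conclusion.** The point holds for the efficacy analysis. Under either reading that gives Section 9.3.1 any effect, it excludes subjects whom Section 9.1 includes, and it discards data that the chosen model could use. A subject withdrawn before hour 24, including for an adverse event, would drop out of the efficacy results.

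The size depends on assumptions the protocol does not supply. If any missing time point counts, and values are missing independently at 2% to 10%, about 17.7 down to 10.6 of 20 subjects remain. If only hour 24 counts, 19.6 down to 18.0 remain. The direction of any bias is not known.

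The counting of replaced subjects is a separate, unresolved inconsistency between Sections 4.4, 6.2.5, 9.2.8 and 9.3.1. Severity: should-fix.

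**What to change.** 1. Replace the exclusion sentence in Section 9.3.1 with: *All observed post-dose values from subjects in the Efficacy population with a baseline value enter the mixed model (likelihood-based, missing at random); no subject is removed for a missing time point.* The baseline condition is needed because the model is for change from baseline, while Section 9.1 does not say when the single IVM measurement must be taken.
2. State that the rule does not restrict the safety analyses.
3. State that replaced subjects stay in every analysis population they qualify for, and report the number replaced, with reasons, by dose level.
4. Reconcile Sections 4.4, 6.2.5, 9.2.8 and 9.3.1 on whether a replaced subject counts in the group of 4 under review and in the 20 treated. Which rule applies is for the sponsor and investigators to decide; the text should give one answer throughout.

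The cost is a few sentences in the protocol and the analysis plan. The one practical downside is that the treated total may slightly exceed 20, and the protocol should say so.
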